### Preparation and evaluation of composite powder

#### Preparation of pearl millet beverage powder and baobab fruit powder

The pearl millet beverage (unfortified) is a popular Ghanaian beverage. The beverage powder will be prepared using a standardised Ghanaian traditional recipe with minor modifications. The pearl millet (*Pennisetum glaucum*) will be sourced in bulk from the local markets in the study area (Kumbungu District). The millet will be winnowed, debris, sand, and stones sieved out. The millet will be stored in airtight containers at room temperature until use^(45)^. Regarding the beverage powder preparation, the pearl millet (700 g) will be first soaked in clean water (900 ml) for 6 h, drained and rinsed. Ginger (50 g), cloves (4 g) and chilli pepper (4 g) will be added to the soaked millet and ground to flour. The flour will be sun-dried (8 h) and milled to fine powder. For the baobab fruit powder, the fruits will be harvested and crushed to remove the outer shell and the pulp separated from the seeds. The pulp will be ground and sieved to obtain the fine powder. Both the pearl millet beverage powder and baobab fruit powder will be kept in airtight and water-proof containers/bags and stored in a freezer until use^(46)^.

#### Formulation and preparation of beverages

Two powder formulations will be made: (1) baobab pulp-fortified pearl millet beverage powder for the intervention group (arm 1) and (2) unfortified pearl millet beverage powder for the control group 1 (arm 2).

Based on the Ghanaian traditional recipe for the beverage (zomkom), the beverage will be prepared by dissolving the powder mix (60 g millet powder enriched with 9 g baobab fruit powder) in chill/cold water (300 ml) with added sugar (8 g), making a total volume of 350 ml. The amount of baobab powder enrichment was determined based on an acceptability test done among adolescent girls (online Supplementary file 1). The sugar content of the beverage (2·2 g/100 ml) is within the acceptable amount of sugar (≤ 2·5 g/100 ml) in beverages that will have no significant negative impact on BMI and other health outcomes^(47,48)^ and the amount of sugar in the beverage per serving per day (8 g/350 ml) is also far lower than the WHO’s daily recommended maximum amount of free sugar intake for children (50 g, equivalent to 10 % of total energy intake)^(49)^. To test the acceptance of the volume of beverage per serving (350 ml), 40 adolescent girls were fed the beverage over 3 days and all participants comfortably consumed all the 350 ml of the beverage in each feeding session.

The RDA of Fe for adolescent girls aged 10–19 years averages at 13·6 mg (8 mg, 15 mg and 18 mg for girls aged 10–13, 14–18 and 19 years respectively)^(50)^. As in similar studies^(51–53)^, the target of this study is to meet closely the average RDA (13·6 mg) of Fe daily for six months. Hence, the intervention group will receive 350 ml of the baobab pulp-fortified beverage containing 13 mgFe (96 % of average RDA), 18·8 mg of vitamin C (30·4 % of average RDA)^(50)^ and 222·1 mg of citric acid, while the control group 1 will receive similar volume of the unfortified beverage containing 12·4 mgFe (91·2 % of average RDA) once daily, five times a week for six consecutive months. Preparation and formulation of the beverage powders will be done in the Diet Practicum Laboratory at the Department of Nutritional Sciences, University for Development Studies, because of its proximity to the study area.

#### Nutritional content, microbiological quality and shelf life

With regards to the nutrient content of the beverage, proximate (protein, fat and carbohydrate), minerals (Fe, Zn, K, Cu, Mg, Na and P) and organic acids (ascorbic and citric acids) content of the beverage per serving per day (350 ml) were evaluated using Association of Official Analytical Chemists^(54)^, atomic absorption spectrometry^(51)^ and high-performance liquid chromatography^(28)^ methods respectively. Table 2 depicts the nutrient content of the fortified beverage per serving per day (350 ml). Based on microbial quality and shelf life (accelerated technique with moisture content as a determinant) evaluations we performed earlier on the composite powder, the powder is microbiologically safe for consumption (online Supplementary file 2) and has a shelf life of 9 months under room temperature. Also, the composite powder’s vitamin C content showed no significant decline (27·9 mg/100 g to 24·7 mg/100 g, *P* = 0·16) after four months of storage at a temperature of 55°C in plastic bags, indicating its stability.

**Table 2. tbl2:** Nutrient content of beverage per 350 ml

Nutrient	Amount per serving (350 ml)
Macronutrients (g)	
Fat	7·5
Protein	9·6
Carbohydrate	46·2
Micronutrients (mg)	
Citric Acid	222·1
Vitamin C	18·8
Fe	13
Cu	2
Zn	4·4
Mn	1·5
Na	41·7
Mg	129·8
K	712·9
P	233·9

### Baseline assessment

A pre-tested structured questionnaire will be employed to document information on participants’ socio-demographic characteristics and dietary consumption patterns. Participants’ anthropometric measurements will be taken to assess their nutritional status (online Supplementary file 3). Biochemical indices such as Hb concentration, serum ferritin and C-reactive protein of participants will also be assessed to diagnose Fe deficiency, Fe deficiency anaemia and anaemia. WHO (2020) currently recommends serum ferritin as an adequate marker of Fe status when assessed along with inflammation/infection markers (C-reactive protein and/or *α*-1 acid glycoprotein) and ferritin adjusted as necessary^(55)^.

#### General characteristics

General characteristics of participants such as age, ethnicity, religion, level of education (class), educational and occupational statuses of their parents/guardians, household size, menarche status and age at menarche will be documented.

#### Dietary assessment

A multiple-pass 24-hour dietary recall, which will be repeated in 20 % of a random subsample (for usual intake)^(56,57)^, will be used to collect dietary information from the participants. The 24-hour dietary recall will be conducted on two non-consecutive days, one weekday and one weekend^(58–60)^. Participants will be asked to recall and describe all foods and drinks consumed in the past 24-hours. The amount of food consumed by each participant will be estimated using household handy measures and converted to grams. The total intake of macronutrients and micronutrients including Fe and vitamin C will be quantified using the Ghana Nutrient Analysis Template^(61)^.

Diet quality of participants will also be assessed by means of dietary diversity score^(62)^. Based on the 24-hour recall, the number of food groups each participant ate from will be documented. The 10 food groups recommended by FAO^(62)^ for assessing dietary diversity score of women will be used. Dietary diversity score will be determined by allocating a score of 1 to each food group consumed and a score of 0 to each food group not consumed and a sum total of all scores calculated. Participants who obtain a score ≥ 5 will be deemed to have met the minimum dietary diversity score^(62)^.

Additionally, participants’ dietary pattern will be determined by assessing their frequency of consumption of various food groups over the preceding month, including foods from animal sources, cereals, legumes, fruits, vegetables, sugar-sweetened beverages and snacks. As the participants are teenagers, their mothers will be invited to be present during dietary data collection to ensure accurate data collection.

#### Anthropometry and anaemia awareness and prevention practices

Height (m) and weight (kg) of respondents will be measured and BMI-for-age z-scores computed. Height of participants will be measured without shoes using a stadiometer (Seca, Germany). Weight will be taken in light clothing and without shoes using an electronic scale (Seca, Germany). BMI-for-age z-scores will be calculated using WHO Anthro Plus software and classified as underweight (< −2 sd), normal (–2 sd to +1 sd), overweight (> +1 sd) and obese (> +2 sd)^(63)^. Regarding knowledge and prevention practices related to Fe deficiency anaemia, the FAO questionnaire^(64)^ will be adapted for the study.

#### Haematological and biochemical assessment

At baseline and end-line, about 5 ml of non-fasting venous blood sample will be collected from each participant by a phlebotomist and analysed for Hb concentration, serum ferritin and C-reactive protein.

##### Determination of haemoglobin status

Hb level of participants will be measured using URIT 12 Hb analyser^(65,66)^. The test strip will be inserted into the URIT 12 Hb analyser and a drop of the drawn whole blood placed on the sample spot of test strip. The Hb results will be recorded to the nearest 0·1 g/dl. For girls aged ≥ 12 years, Hb levels < 8 g/dl, 8–10·99 g/dl, 11–11·9 g/dl and ≥ 12 g/dl will be categorised as severe anaemia, moderate anaemia, mild anaemia and normal, respectively^(67)^. For girls aged < 12 years, Hb levels < 8 g/dl, 8–10·9 g/dl, 11–11·4 g/dl and ≥ 11·5 g/dl will be categorised as severe anaemia, moderate anaemia, mild anaemia and normal, respectively^(68)^.

##### Determination of serum ferritin and C-reactive protein

The whole blood will be put in the gel-coated serum separator vacutainers and preserved at 4°C in an ice chest containing cold packs while in the field. The serum will be separated by means of a centrifuge at 500 rpm for 5 min at refrigerated temperature. The separated serum will be aliquoted and frozen at −80°C. The serum will be transported to the testing laboratory on frozen ice packs in an ice chest, when time is due for analysis. The ELISA technique will be used to assess serum concentrations of ferritin and C-reactive proteins. Fe deficiency will be defined as serum ferritin concentrations < 15 ug/l for healthy individuals and < 70 ug/l for individuals with inflammation/ infections^(55)^ and inflammation/infection as C-reactive proteins > 5 mg/l^(69)^.

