### Sample size

The formula employed for the sample size estimation is: N = 2S

(

+

/

^(36)^

where N is sample size

sd is standard deviation; estimated to be 20·1 μg/l for serum ferritin^(37)^ and 1·2 g/dl for Hb (anaemia)^(32)^.

 = 1·96 (From Z table) at a precision of 5 % and CI of 95 %.

 = 0·84 (From Z table) at 80 % power.

d is effect size; estimated to be 9·4 μg/l for serum ferritin^(38)^ and 0·65 g/dl for Hb (anaemia)^(39)^.

Sample size (Serum ferritin): N = 2

(

*+*

*/*

= 72

Sample size (Hb): N = 2

(

*+*

*/*

= 53

The larger sample size (N = 72) of the 2 variables (serum ferritin and Hb) will be used for the study.

As a cluster randomised controlled trial, cluster design effect has to be considered in the sample size calculation to improve the power and precision of the study^(40,41)^. The required sample size for a cluster randomisation trial is obtained by multiplying the sample size of the individual randomisation trial (N = 72) by the design effect^(42,43)^. Design effect = 1 + intra-cluster correlation (m-1), where m is the average cluster size. An estimated intra-cluster correlation of 0·0009^(44)^ will be used. The average size of each cluster (school) in the study district is estimated to be 55 adolescent girls, with the number of anaemic adolescent girls in each school estimated to be 43^(32)^, thus m = 43. Design effect = 1 + 0·0009(43–1) = 1·037. Hence, considering the design effect of 1·037 and 15 % attrition rate, the sample size will be 86 participants per arm (258 participants for the 3 arms, with 43 participants to be chosen from each school).

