### Outcome measures

The primary outcomes will be serum ferritin (ug/l) and Hb (g/dl) concentrations of participants. Secondary outcomes will be prevalence of Fe deficiency, Fe deficiency anaemia and BMI-for-age.

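### The stated spin for the ferritin serum, 500 rpm for 5 min in gel separator tubes, gives only about 22–70 × g; it should be verified and restated as a force

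*Protocol article*

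**What the plan says.** The section on determination of serum ferritin and C-reactive protein fixes the tube, the spin, the storage and the assay:

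- Tube: "The whole blood will be put in the gel-coated serum separator vacutainers". It is then held at 4°C in the field.
- Spin: "The serum will be separated by means of a centrifuge at 500 rpm for 5 min at refrigerated temperature".
- Storage: "The separated serum will be aliquoted and frozen at −80°C".
- Assay: "The ELISA technique will be used to assess serum concentrations of ferritin and C-reactive proteins".

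The speed is given in revolutions per minute only. The section states neither a rotor radius nor a force.

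Under Outcome measures: "The primary outcomes will be serum ferritin (ug/l) and Hb (g/dl) concentrations of participants". Ferritin also sets the sample size, because its requirement of 72 per arm exceeds the 53 for haemoglobin before the design effect and attrition. It also defines iron deficiency, a secondary outcome: "Fe deficiency will be defined as serum ferritin concentrations < 15 ug/l for healthy individuals and < 70 ug/l for individuals with inflammation/ infections".

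**The concern.** A gel separator tube works only if the spin is strong enough to move the gel between clot and serum. Revolutions per minute do not state that strength without a rotor radius, and 500 rpm looks too slow for any ordinary bench rotor.

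If the line is followed literally, the layer taken off as serum may still hold cells. Freezing can break cells open, and their ferritin would then be measured by the ELISA as serum ferritin. This mechanism is general laboratory reasoning and is not stated in the protocol.

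What would be at stake is the measurement quality of one of the two primary outcomes, the one on which the sample size rests, and of the iron deficiency and iron deficiency anaemia classifications derived from it.

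**Working it through.** **Inputs from the protocol article.** Speed 500 rpm, time 5 min, refrigerated, gel separator tubes (ferritin and C-reactive protein section). Ferritin difference 9.4 µg/l and SD 20.1 µg/l (Sample size).

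**Assumptions, not in the document.** Rotor radius r of 10–20 cm for an ordinary bench centrifuge, with 8–25 cm as the wider range. Force needed to form a gel barrier of 500–2000 × g, to be checked against the tube maker's instructions.

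The protocol states no force, so there is no figure of its own to reproduce at this step.

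**Step 1: force at the stated speed.**

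RCF = 1.118 × 10⁻⁵ × r (cm) × rpm². At 500 rpm, 1.118 × 10⁻⁵ × 250,000 = 2.795, so RCF = 2.795 × r.

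| r (cm) | RCF (× g) |
|---|---|
| 8 | 22.4 |
| 10 | 28.0 |
| 15 | 41.9 |
| 20 | 55.9 |
| 25 | 69.9 |

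Computing the force from angular velocity (ω²r / 9.80665, with ω = 500 × 2π/60) gives the same values to within 0.1 × g.

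**Step 2: does the conclusion depend on the assumed radius or benchmark?**

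The radius needed to reach a given force at 500 rpm is force / 2.795:

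- 500 × g: 179 cm
- 1000 × g: 358 cm
- 2000 × g: 716 cm

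The most favourable pairing, a 25 cm rotor and a 500 × g requirement, still gives only 69.9 / 500 = 14% of the force. The conclusion therefore does not turn on the exact value of either assumption within these ranges.

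**Step 3: what the number may have been meant to be.**

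Speed for a given force is √(RCF / (1.118 × 10⁻⁵ × r)):

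| Force | r = 10 cm | r = 15 cm | r = 20 cm |
|---|---|---|---|
| 1000 × g | 2991 rpm | 2442 rpm | 2115 rpm |
| 2000 × g | 4230 rpm | 3453 rpm | 2991 rpm |

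Force goes with the square of speed. A dropped zero (5000 rpm) would mean (5000/500)² = 100 times the force, or 2795–5590 × g at 10–20 cm. A unit slip (500 × g printed as 500 rpm) would sit at the bottom of the assumed range. The printed line does not show which, if either, occurred.

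**Step 4: how an error would enter the results.**

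The ferritin sample size reproduces: 2 × (20.1 × 2.8 / 9.4)² = 71.7, rounded up to 72. The SD enters as a square. Extra assay scatter with standard deviation s, beyond what is already in the 20.1 µg/l, would multiply the required number by 1 + s²/20.1². The document gives nothing from which s could be obtained.

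An upward shift common to all arms would cancel in the difference between arm means. It would not cancel against the fixed 15 µg/l and 70 µg/l cut-offs, where it could move some participants across the line.

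**The case against.** The strongest case against is that the required force is not in the protocol. No tube maker, rotor or minimum force is named, and the route from residual cells to raised ferritin is also external. This stands in part. The benchmark has to be labelled as an assumption, and the size of any ferritin error stays unknown. It does not remove the point, because the stated speed falls short even of the lowest benchmark in the range.

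A second objection is that the number is probably a slip and that the samples were, or will be, spun properly. That is a live possibility, and the text goes on to speak of separated serum. It still calls for correction, since the printed line is what a reader would follow or replicate.

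A third is that a journal article condenses laboratory detail. That disposes of one tempting reading, namely that blood is chilled with no clotting step. The article is silent on clotting, and silence in a condensed text does not show that the step is skipped. Clotting would also hold back many of the cells. The speed is different, because it is stated.

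Two further readings go beyond the documents:

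- **That iron deficiency will be undercounted.** An upward shift could have that effect, but neither its occurrence nor its size can be shown, and scatter alone can move participants across a cut-off in either direction.
- **That poor separation will appear as an arm difference, because each arm has only two schools.** The protocol describes one procedure for everyone at both visits, and nothing in it suggests that processing differs by school or day.

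Haemoglobin, the other primary outcome, is read from whole blood and is unaffected.

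**Conclusion.** The point holds as a query on a stated laboratory setting. As printed, 500 rpm gives about 28–56 × g at a radius of 10–20 cm and no more than about 70 × g at 25 cm. The force assumed necessary is 500–2000 × g. The setting is implausible for the tube named, and it applies to a primary outcome.

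If it is followed, separation may be incomplete and ferritin may carry added noise or an upward shift. The size cannot be derived from the document. Noise or a common shift is more likely than a bias between arms. The conclusion rests on the assumed rotor radius and gel requirement, and it is robust across the ranges shown. It does not establish that any sample has been compromised.

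**What to change.** Verify the setting actually used. In the ferritin and C-reactive protein section, replace the 500 rpm, 5 min setting with a force in × g, a time and a temperature that meet the tube maker's instructions. State that the same settings apply at baseline and end-line in all six schools, and that serum is aliquoted only when the gel barrier is intact.

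The study period runs from February to October 2024, so some samples may already have been processed. If the printed figure was a slip, correcting the record is enough. If samples were spun at the stated speed, report this as a limitation of the ferritin outcomes. If only the later visit was then corrected, say so, because the within-arm comparison of baseline with end-line would mix two procedures.

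The cost is one corrected line and a few more minutes per batch.

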#### Deworming

All participants will be treated against intestinal parasites by the study physician using a single dose of albendazole 400 mg chewable tablets. The first dose will be given 2 weeks prior to the commencement of feeding and a second dose given at midpoint of the intervention^(70)^.

#### Malaria screening and treatment

All participants will be tested for malaria using the malaria rapid diagnostic kits at baseline and halfway. Participants who test positive for malaria will be treated by the study physician using artemether-lumefantrine 20 mg/120 mg in 6-dose regimen over a 3-day period as recommended by Ghana Health Services^(71)^.

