Fe deficiency is the main cause of anaemia among adolescent girls^(7)^. Adolescence is a period of fast growth with an acute rise in blood volume, lean body mass and red blood cell mass, which results in a surge in Fe requirement for the synthesis of Hb and myoglobin^(8)^. Adolescent girls are more vulnerable to Fe deficiency compared to their male counterparts because of the monthly loss of Fe through menstruation^(9)^. They are three times more likely to be Fe deficient as compared to adolescent boys^(6)^. Other factors such as poor bioavailability of dietary Fe, low dietary intake of Fe, infectious diseases and parasitic infections also contribute to Fe deficiency^(8,10)^. The determinants of anaemia are context-specific^(11)^, and in Ghana, some of the contextual determinants of anaemia include poor nutritional knowledge, intestinal worms, diarrhoea, food, malaria and poor dietary intake^(12)^. The diets of adolescents, particularly rural adolescents in Ghana, are largely plant-based^(13),^ and bioavailability of Fe from such diets is limited^(14)^; hence, most adolescent girls are unable to meet the increased Fe requirements during adolescence caused by high growth spurt and the loss of Fe each month through menstruation.

In Ghana, Fe food fortification and Fe supplementation are the main interventions in place to address Fe deficiency anaemia among adolescent girls^(15)^. However, these approaches have challenges in terms of acceptability, sustainability and affordability in developing countries^(16–19)^. Food-to-food fortification which utilises locally available foods is recommended as a good alternative measure for addressing micronutrient deficiency in developing countries, as it overcomes the aforementioned challenges of the conventional approaches^(16,17)^. Food-to-food fortification is the addition of a locally available and accessible micronutrient dense food to another locally available and accessible food to enhance the bioavailability of micronutrients to populations^(17)^. In Ghana, food-to-food interventions have been shown to improve Fe status of lactating mothers^(20)^ and anaemia status of children aged 6–9 years^(21)^. However, there is scanty data on food-to-food fortification interventions for improving the Fe status of adolescent girls in Ghana.

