### Sampling procedure

A multi-stage cluster sampling technique will be employed in the study. Six communities in the district will be selected through simple random sampling. A school from each of the selected communities will be chosen through simple random sampling, making six schools in all. In the study schools (clusters), all adolescent girls in Upper Primary (Primary 4–6) and Junior High School will be screened based on the inclusion and exclusion criteria to identify eligible participants. Simple random sampling will be used to select the desired number of participants from the eligible participants. The study period is from February to October 2024. Figure 1 depicts the flow chart of the trial.

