### Study timeline

The protocol was developed from October 2022 to February 2023. Initial ethical approval and protocol amendment approval were obtained on 21st April 2023 and 10th January 2024, respectively. The treatment duration (Intervention) of the trial is six months. The specific timelines for participants’ enrolment, interventions, assessments, data analysis and dissemination of results are depicted in Table 1.

**Table 1. tbl1:** Schedule of enrolment, interventions, assessments, data analysis and results dissemination

	Study period								
	Enrolment	Allocation	Treatment period (6 months)						Close-out
Timepoint (t) (months)	*−t* _ *1* _	0	*t* _ *1* _	*t* _ *2* _	*t* _ *3* _	*t* _ *4* _	*t* _ *5* _	*t* _ *6* _	*t* _ *7–11* _
Enrolment:									
Eligibility screen	X								
Informed consent	X								
Allocation		X							
Interventions:									
Fortified beverage									
Unfortified beverage									
Fe-folate tablets									
Assessments:									
Socio-demographics	X								
Dietary intake	X								X
Anthropometry	X								X
Anaemia awareness and prevention	X								
Malaria testing	X					X			
Hb	X								X
Serum ferritin	X								X
C-reactive protein	X								X
Data analysis									X
Results dissemination									X

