### Mid-way treatment

All participants will also be re-treated against intestinal parasites at mid-way using a single dose of albendazole 400 mg chewable tablets. Participants will also be re-tested for malaria at midpoint. Those who test positive for malaria will be treated by the study physician.

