### Post-intervention assessment

At the end of the feeding intervention, post-intervention assessment will be done immediately. Dietary intake, anthropometry and the biochemical indices will be reassessed.

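### Malaria, named in the protocol as a determinant of anaemia, is not tested at end-line when both primary outcomes are read, so malaria at that reading cannot be described by arm

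*Protocol article*

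**What the plan says.** The introductory text of the protocol article gives the local causes of anaemia: "some of the contextual determinants of anaemia include poor nutritional knowledge, intestinal worms, diarrhoea, food, malaria and poor dietary intake".

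The section Malaria screening and treatment sets the test times: "All participants will be tested for malaria using the malaria rapid diagnostic kits at baseline and halfway". The section Mid-way treatment repeats the second one: "Participants will also be re-tested for malaria at midpoint". In Table 1 (Study timeline) the row "Malaria testing" has a mark at enrolment and one during treatment. It has none at close-out, where Hb, ferritin and CRP are all marked.

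The section Post-intervention assessment lists what is repeated at the end: "Dietary intake, anthropometry and the biochemical indices will be reassessed". Under Baseline assessment and under Haematological and biochemical assessment, those indices are Hb, ferritin and CRP. Malaria is not among them.

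Under Outcome measures: "The primary outcomes will be serum ferritin (ug/l) and Hb (g/dl) concentrations of participants". The Statistical analysis section compares these by one-way ANOVA across the three arms and by paired t tests within arms. It also plans regressions on covariates, which it does not name.

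**The concern.** Malaria is measured alongside the baseline reading of Hb and ferritin but not alongside the end-line reading on which the trial's conclusion rests. The protocol itself treats infection as something that distorts ferritin: the Fe-deficiency cut-off rises from 15 to 70 µg/l when CRP exceeds 5 mg/l. It also treats malaria as a cause of low Hb.

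Each arm consists of two schools, each from a different community. If malaria happens to be commoner in one arm's communities at end-line, that arm's mean Hb would be lower and its mean ferritin probably higher for reasons unrelated to the product. With so few clusters, randomisation cannot be relied on to even this out. Without an end-line test the investigators could neither show such an imbalance nor rule it out, and no analysis plan can recover a test that was not taken.

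**Working it through.** **1. The schedule.** The four places that bear on it agree.

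| Place in the protocol article | Malaria test |
|---|---|
| Malaria screening and treatment | Baseline and halfway |
| Mid-way treatment | Midpoint |
| Table 1 | Enrolment and one treatment month (t4 by column count) |
| Post-intervention assessment | Not listed |

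The Study timeline section states: "The treatment duration (Intervention) of the trial is six months". A halfway test leaves 6 − 3 = 3 months before end-line. The Table 1 mark gives 2 to 3 months, depending on how t4 is read.

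**2. The planned effects used as yardsticks.** The Sample size section takes SD 20.1 µg/l and effect 9.4 µg/l for ferritin, and SD 1.2 g/dl and effect 0.65 g/dl for Hb, with 1.96 + 0.84 = 2.8.

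- Ferritin: 2 × (20.1 × 2.8 / 9.4)² = 71.7, so 72 (stated 72).
- Hb: 2 × (1.2 × 2.8 / 0.65)² = 53.4 (stated 53).
- Design effect: 1 + 0.0009 × 42 = 1.0378. Then 72 × 1.0378 × 1.15 = 85.9, so 86 per arm (stated 86).

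The plan's figures reproduce. The yardsticks are 0.65 g/dl and 9.4 µg/l.

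**3. Possible shift in the Hb comparison.** Shift = (difference between arms in end-line malaria prevalence) × (mean Hb reduction in an infected girl). The documents give neither input, so both are assumed: 10 to 30 percentage points, and 0.5 to 1.0 g/dl.

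| Difference between arms | Hb lower by 0.5 g/dl | Hb lower by 1.0 g/dl |
|---|---|---|
| 0 points | 0 | 0 |
| 10 points | 0.05 g/dl (8 % of 0.65) | 0.10 g/dl (15 %) |
| 20 points | 0.10 g/dl (15 %) | 0.20 g/dl (31 %) |
| 30 points | 0.15 g/dl (23 %) | 0.30 g/dl (46 %) |

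**4. Ferritin.** The documents give no figure here either. As an illustration only, suppose infected girls read 10 to 40 µg/l higher and the arms differ by 10 to 20 points. The shift is then 0.10 × 10 = 1 µg/l to 0.20 × 40 = 8 µg/l, or 11 % to 85 % of 9.4. A range that wide shows the size is unknown.

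**5. What else is recorded at end-line.** CRP is measured, but it does not separate malaria from other inflammation. Its only stated use is to choose the ferritin cut-off for Fe deficiency, a secondary outcome. It is not applied to Hb or to mean ferritin in the stated ANOVA.

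**The case against.** The documents do not contradict themselves on this point, and no figure in them is wrong. Several stronger conclusions that a reader might draw are not supported.

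- *That malaria after the midpoint goes wholly undetected and unmanaged.* The Adverse events section has the study physician assess participants every week and has all adverse events documented. Symptomatic malaria could be picked up that way. What remains is infection that is asymptomatic or not reported.
- *That the time of year biases the product comparison.* "The study period is from February to October 2024", so baseline and end-line fall at different times of year. But the arms run in parallel in one district, and a seasonal change common to all arms cancels between them. It touches only the within-arm paired tests.
- *That a CRP-driven change in Fe-deficiency status illustrates the gap.* The two cut-offs are a deliberate rule, and a malaria test would not alter the classification.
- *That an imbalance would leave no trace.* Lower Hb with higher ferritin and CRP in one arm would be a warning sign, though not one specific to malaria.
- *That one end-line test would capture all malaria since the midpoint.* It shows infection at that time, not earlier episodes.

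It is also fair to say that two schools per arm leaves every school-level factor poorly balanced, and that an end-line malaria test does not cure this. The gain is mainly descriptive. Not naming covariates in a condensed article is not counted as a fault here.

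The narrower point stands: a named cause of the primary outcome is not tested when that outcome is read, and this cannot be repaired later.

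**Conclusion.** The point holds as a cheap improvement, not as an error in the plan. Malaria at end-line that is asymptomatic or unreported cannot be described by arm, and because each arm is only two communities, malaria that differs by community could shift the Hb and ferritin comparisons.

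The size is not known. The Hb shift of 0.05 to 0.30 g/dl (8 % to 46 % of the planned effect) rests entirely on assumed inputs, and its upper end combines both upper extremes. It is zero if malaria is equal across arms, but without an end-line test the trial could not show that it was equal.

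**What to change.** - Add the same rapid test to the Post-intervention assessment section and to the close-out column of Table 1, using the venous sample (about 5 ml) already drawn there.
- Report end-line malaria by school and by arm.
- Include baseline malaria status, which is already collected, as a covariate in the between-arm model for Hb and ferritin, in place of an unadjusted one-way ANOVA.
- Show a clearly labelled sensitivity analysis of Hb and ferritin by end-line malaria status. It should not replace the primary analysis, because end-line malaria arises after randomisation and selecting on it can itself introduce bias.

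The clinical handling of positive results is for the sponsor to decide.

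Cost: up to 3 × 86 = 258 rapid kits, one more mark in Table 1 and a few minutes per girl, with no extra visit or blood draw. Limits: the test shows infection at end-line only, and neither it nor the covariate adjustment removes the imbalance risk of two schools per arm.
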